### Methods in analysis to handle protocol non-adherence and any statistical methods to handle missing data {20c}

Given the safety-oriented and mechanistic nature of the trial, all analyses will be conducted per protocol; however, as a sensitivity analysis, missing laboratory data will be imputed by multiple imputation to assess the robustness of study results.

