### Criteria for discontinuing or modifying allocated interventions {11b}

Participants may elect to withdraw from the trial at any time for any reason. Participants may be withdrawn by the study team if they experience any new-onset, moderate or severe adverse events from the intervention. Any a priori-specified critical lab value observed and confirmed on repeat analysis and attributable to the intervention may also result in participant withdrawal. The trial will be halted if >20% of all participants demonstrate laboratory abnormalities in per the criterion listed *or* experience adverse events of moderate or greater severity which are new from baseline or progressively worsening.

No modifications of intervention dose or frequency of administration are allowed, and participants will be considered non-adherent and withdrawn from the trial if deviations from the dosing standard are reported to the study team. As XN was demonstrated as safe and tolerable in healthy adults at the same dosage and length of time in our phase I study [15], and is considered Generally Recognized as Safe [20], it is not anticipated that serious harms will require early discontinuation of the product or medical intervention to address the issue.

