### Strategies to improve adherence to interventions {11c}

Adherence will be monitored throughout the trial at weekly visits through verbal query and formally assessed at the week 4 and closeout visits by capsule count. Participants will be provided with sufficient study product for 5 weeks (35 capsules) at randomization and week 4 in anticipation of potential scheduling changes and/or unexpected losses. Participants will be considered adherent by taking >80% of expected doses throughout their participation in the trial. Participants will be provided suggestions to improve adherence such as daily phone alarms, consistent timing, reminder notes, etc. Returned study product will be stored in a locked cabinet in a locked room for future quality assessment.

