### Outcomes {12}

The primary outcomes of the phase II trial include changes in laboratory toxicology measures, vital signs (blood pressure and heart rate), and AEs (Table 1). Assessment of laboratory measures to determine safety includes review for new-onset abnormalities (confirmed with repeat testing at the following clinical visit or as soon as possible following closeout, as applicable), including new-onset clinically significant elevation of liver function tests [aspartate transaminase (AST), alanine transaminase (ALT), bilirubin or alkaline phosphatase], new-onset anemia, elevations in creatinine, and/or reductions in estimated glomerular filtration rate (eGFR). Elevations of liver function tests will be considered “significant” if (1) abnormal per laboratory reference ranges and (2) represent a 25% deviation from previously observed values. New-onset anemia will be considered “significant” if (1) hemoglobin < 14 g/dL (140 g/L), hematocrit < 42% (< 0.42), or RBC < 4.5 million/mcL (< 4.5 × 10^12^/L) (for men); or hemoglobin < 12 g/dL (120 g/L), hematocrit < 37% (< 0.37), or RBC < 4 million/mcL (< 4 × 10 ^12^/L) (for women); *and* (2) values represent a 10% change or more from *baseline* values; *and* (3) values remain abnormal with repeat testing within 2 weeks. This threshold reduces reporting of new “borderline” abnormal values for participants with “high normal” baseline values. For elevations of creatinine, “significant” will be evaluated as greater than a 20% increase from *baseline* values, whereas reductions in eGFR will be considered as “significant” if greater than a 20% decrease from *baseline* values. A brief clinical interview will be conducted and recorded for all laboratory abnormalities not present at baseline to provide context, i.e., new-onset anemia tied to increased diarrheal episodes, etc. Serum calcium, potassium, and sodium; ɣ-glutamyl transferase (GGT); and blood urea nitrogen (BUN) to creatinine ratio (BUN:Cr) will also be collected to monitor electrolyte balance and provide additional measures of liver and kidney function, respectively.

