## Data collection and management

### Plans for assessment and collection of outcomes {18a}

Data collected from all participant interactions will be recorded on paper case report forms (CRFs) with electronic transcriptions stored in REDCap® [21, 22]. Physical data will be stored in a locked cabinet, in a locked document room, or in a building accessible only via badge or key. Electronic data will be stored in a de-identified manner and entered on a password-protected device by study staff into REDCap®. All data will be collected by study staff by verbal query or physical assessment other than the PROMIS-29 questionnaire which the patient will self-report directly into REDCap® on a password-protected tablet. All specimens will be labeled using a convention that includes participant ID, visit number, date stored, and specimen type.

Hematologic safety parameters in this study include those associated with liver function (AST, ALT, alkaline phosphatase, bilirubin, and GGT); kidney function (eGFR, BUN, creatinine, and BUN:Cr); general hematology (red blood cell count, white blood cell count, hematocrit, and hemoglobin); and electrolytes (sodium, potassium, calcium, and chloride). Spontaneous, self-reported, and serious adverse events will also constitute the safety and tolerability profile of XN. Retention, intervention adherence, and self-reported quality of life, measured through the Patient-Reported Outcomes Measurement Information System 29-item questionnaire (PROMIS-29) [23], will be considered measures of tolerability. All parameters will be collected at each visit and intervention adherence will be monitored at 4 weeks from baseline and at closeout.

Clinical activity will be evaluated using the Crohn’s Disease Activity Index (CDAI). The CDAI is a validated index based on clinical observations, laboratory values, and patient-reported outcomes [24, 25]. While there remains some controversy over the use of the CDAI, it correlates with other accepted indexes of clinical activity and some patient-reported subsets and further correlates with endoscopic activity indexes [26]. Abdominal examinations for masses will be performed by a licensed clinician.

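### The primary safety comparison is fixed as per protocol, while withdrawal can depend on adverse events, laboratory toxicity and dosing deviations, so harms can be understated

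*Protocol article*

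**What the plan says.** The section on non-adherence and missing data {20c} sets one basis for every analysis: "Given the safety-oriented and mechanistic nature of the trial, all analyses will be conducted per protocol". It offers one safeguard: "as a sensitivity analysis, missing laboratory data will be imputed by multiple imputation to assess the robustness of study results".

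The section Outcomes {12} makes safety the primary question: "The primary outcomes of the phase II trial include changes in laboratory toxicology measures, vital signs (blood pressure and heart rate), and AEs".

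The discontinuation criteria {11b} give three routes out of the trial that concern this point:

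- Adverse events, at the team's discretion: "Participants may be withdrawn by the study team if they experience any new-onset, moderate or severe adverse events from the intervention".
- Laboratory values, at the team's discretion: "Any a priori-specified critical lab value observed and confirmed on repeat analysis and attributable to the intervention may also result in participant withdrawal".
- Dosing deviations, with no discretion: "participants will be considered non-adherent and withdrawn from the trial if deviations from the dosing standard are reported to the study team".

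The adherence section {11c} uses a different standard: "Participants will be considered adherent by taking >80% of expected doses throughout their participation in the trial".

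The per-protocol set is not defined further, and no section names an all-randomised or all-treated set for safety.

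**The concern.** In a safety trial, a participant who reacts badly to the product is the one who most needs to be counted. A per-protocol set keeps those who followed the protocol. Here, staying in the protocol depends partly on not having a moderate or severe event judged to come from the product, not having a confirmed critical laboratory value, and not departing from the dosing schedule. The first two are primary outcomes. The third can be a consequence of poor tolerability.

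Exclusion can therefore be informative, and its direction favours the trial's hypothesis that xanthohumol is safe and tolerable. The stated reason for the choice, the trial's safety orientation, argues for the opposite choice: a safety comparison normally keeps everyone who was exposed.

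**Working it through.** **1. Numbers the plan gives.** Sample size {14} needs 12 per arm and allows 25% attrition: 24 / (1 − 0.25) = 32 randomised, or 16 per arm. This reproduces the plan's figure. It also means that up to 8 of 32 participants could be missing from the analysis without exceeding what was planned.

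**2. Limit on plausible event rates.** The discontinuation criteria {11b} halt the trial if more than 20% of all participants have qualifying laboratory abnormalities, or new or worsening events of at least moderate severity. The documents give no expected event rates, so rates must be assumed, and they should stay under this limit. Assume 25% on xanthohumol and 10% on placebo. With 1:1 allocation the overall rate is (25% + 10%) / 2 = 17.5%, which is under 20%.

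**3. Effect of excluding participants with events.** If the true rate is *p* and a fraction *f* of participants with events is excluded, the observed rate is *p*(1 − *f*) / (1 − *pf*).

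| Fraction excluded | Xanthohumol | Placebo | Difference |
|---|---|---|---|
| 0 | 25.0% | 10.0% | 15.0 points |
| 0.25, both arms | 0.1875/0.9375 = 20.0% | 0.075/0.975 = 7.7% | 12.3 points |
| 0.5, both arms | 0.125/0.875 = 14.3% | 0.05/0.95 = 5.3% | 9.0 points |
| 0.75, both arms | 0.0625/0.8125 = 7.7% | 0.025/0.925 = 2.7% | 5.0 points |
| 0.5, xanthohumol only | 14.3% | 10.0% | 4.3 points |

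**4. How many exclusions this takes.** At *f* = 0.5 in both arms, the expected number excluded is 16 × 0.25 × 0.5 = 2 on xanthohumol and 16 × 0.10 × 0.5 = 0.8 on placebo. That is 2.8 of 32, or about 9%, well inside the 25% allowance.

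**5. Scale.** The bias toward no harm is on the difference scale. With equal exclusion fractions the ratio does not shrink: 25/10 = 2.5 becomes 14.3/5.3 = 2.7. If exclusion falls only on xanthohumol, the ratio drops to 14.3/10 = 1.43. Hypotheses takes a frequency on xanthohumol no more than 50% greater as support for safety. Read as a ratio, 1.43 would pass and the true 2.5 would not.

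**6. Who is in the set.** Eight weeks of one capsule a day is 56 doses. Under {11c}, 45/56 = 80.4% is adherent and 44/56 = 78.6% is not, so a participant may miss 11 doses and remain adherent. Under {11b}, a reported deviation leads to withdrawal. A participant with a few missed and reported doses is adherent under one section and may be withdrawn as non-adherent under the other.

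**7. Reach of the sensitivity analysis.** Multiple imputation is planned for laboratory data. Adverse events and vital signs, which are also primary outcomes, and CDAI are outside it.

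**The case against.** The strongest reply is that leaving the trial is not the same as being deleted from the analysis. The per-protocol set is undefined, and its detail may properly sit in the statistical analysis plan. The article nowhere says that data recorded before withdrawal are discarded. Other sections keep harms in view: events are collected spontaneously and at each biweekly visit {12} and compared between groups {22}, new symptoms are followed up {30}, and the data and safety monitoring board sees significant laboratory abnormalities {20a}. This stands as a limit on certainty. It does not remove the point, because none of these sections names a population that overrides an unqualified statement about all analyses.

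A reader might also infer more than the text supports:

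- *That participants with adverse events are withdrawn as a rule.* Withdrawal for events and laboratory values is discretionary and tied to the intervention. Only the dosing-deviation rule is unconditional. A result in which every event is excluded, and the arms look equally clean, would need every discretionary withdrawal to be exercised.
- *That imputation restores no withdrawn participant.* Missing laboratory data may arise largely from withdrawals, so the imputation may bring some of them back for laboratory outcomes. The document does not settle this.
- *That retention is biased in the same way.* The data collection section {18a} lists "Retention, intervention adherence, and self-reported quality of life" as tolerability measures. Retention is naturally counted over all randomised participants, so it need not be affected.
- *That a single missed capsule ends participation.* With a 1% chance of missing each dose, 1 − 0.99^56 = 43% of participants would miss at least one. That becomes a withdrawal rate only if every missed capsule is a deviation and is reported. The clause follows a ban on changing dose or frequency and can be read as covering altered dosing only. Forgetfulness unrelated to arm would also cost numbers without favouring either arm.
- *That the gap between arms is very large.* Assumed rates such as 40% and 10% average 25%, above the protocol's own halting limit.

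**Conclusion.** The point holds as a risk of bias created by the stated analysis basis. All analyses, including the primary safety comparison, are per protocol; withdrawal can depend on the primary outcome or on its consequences; and nothing in the plan recovers adverse events, vital signs or CDAI for those excluded. Harms *can* drop out of the comparison; the documents do not show that they will.

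For size, under assumed rates of 25% and 10% the difference of 15 points falls to about 9 if half of the participants with events are excluded. Over exclusion fractions of a quarter to three quarters in both arms, it falls to between about 12 and 5 points. The rates and fractions are assumptions. The result also assumes that a withdrawn participant is left out of the per-protocol set altogether. The contradiction between {11b} and {11c} needs no assumption about rates, and it leaves the membership of the set unclear.

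**What to change.** 1. Define the primary safety population as all randomised participants who took at least one capsule, by arm. Count all adverse events and laboratory values to week 8, whether recorded before or after product is stopped or the participant is withdrawn.
2. Analyse CDAI and the biomarkers as randomised. Keep per protocol as a supportive analysis, with its membership defined.
3. Continue scheduled outcome collection after product is stopped, where the participant agrees.
4. Reconcile the withdrawal rule for dosing deviations {11b} with the adherence threshold {11c}, so that membership of the per-protocol set is unambiguous.

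The cost is a change to the analysis wording and a short amendment on data collection, with no added participants. The safety figures may look slightly less favourable. Trial status reports 15 participants already completed, so continued collection can help only those still to be followed. The new analysis population can cover everyone, provided it is fixed before unblinding.

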### Plans to give access to the full protocol, participant-level data, and statistical code {31c}

There are no plans for granting public access to the full protocol, participant-level dataset, or statistical code.

## Oversight and monitoring

### Composition of the coordinating center and trial steering committee {5d}

Clinical investigators, study coordinators, and the clinical site PI will meet on a weekly basis to discuss ongoing business associated with the trial. Amendments to the trial protocol will be sent to the appropriate agency [NCCIH, US FDA, and/or the NUNM Institutional Review Board (IRB)] according to their required timeline. Annual reviews of the trial’s protocol and progress will occur through the NUNM IRB. All study team members will meet regularly to discuss trial developments and administration. The study coordinator will maintain minutes of these meetings, which may be brandished upon request of the DSMB or third-party auditor.

### Composition of the data monitoring committee, its role, and reporting structure {21a}

The DSMB will be composed of a medical doctor, a doctor of osteopathy, a biostatistician, and a toxicologist. The DSMB will review regular reports produced by the study team to ensure safe and responsible conduct of the trial and make any determination of discontinuation. Final reports from the DSMB will be reviewed by the NUNM IRB during annual continuing reviews for approval renewal of trial operations.

### Adverse event reporting and harms {22}

Adverse events will be assessed and graded according to severity at each biweekly clinical visit beginning at the baseline visit, as well as accepted via spontaneous report. Self-reported adverse events will be administered by verbal query through a standardized multi-system questionnaire based on the National Cancer Institute’s Common Technology Criteria for Adverse Events v4.0. Adverse events reported between study visits will be termed “spontaneous adverse events” and graded in a similar manner according to self-reported adverse events according to severity and duration. If an adverse event is of moderate or greater severity, the study team will coordinate with the patient’s physician and develop and document a response or monitoring plan.

Adverse events, both self-reported and spontaneous, will be detailed according to severity and length of duration and compared between groups. The presence of symptoms at baseline will inform the attributability of any symptom to the intervention. Worsening or new-onset symptoms after baseline will be considered potentially attributable to the intervention and will be determined according to prevalence in each group and a case-by-case basis by the study team and DSMB.

### Frequency and plans for auditing trial conduct {23}

Third-party audits and regular DSMB meetings will occur at half-enrollment (initiated after at least 12 participants but no more than 17 have completed the trial) and upon completion of the trial, or per requirements of the NCCIH.

### Plans for communicating important protocol amendments to relevant parties {25}

Potential modification to the protocol, study staff, or trial operations will be submitted to the NUNM IRB for review and approval. Upon approval, any major modifications to eligibility criteria will be submitted to NCCIH and the FDA for review and approval. Upon approval by these agencies, any trial registries will be subsequently updated reflecting these changes.

### Dissemination plans {31a}

Trial results will be shared to participants upon publication of any relevant manuscripts. Publication of safety and tolerability findings and secondary outcomes may be published separately. Additionally, patient advocacy and support groups such as the Crohn’s and Colitis Foundation will be contacted to provide synopsized findings and publications upon request.

## Discussion

In this article, we present the protocol for a phase II trial designed to measure the safety and tolerability profile of XN over an 8-week period in adults with clinically active CD. XN has demonstrated regulatory effects on intestinal permeability via FXR [12, 13], reduction of inflammatory cytokine production through inhibitory actions on NFκB and modulation of FXR and NRF2 [8–13], and modulation of the gut microbiome through its prebiotic activity in non-human models [6, 7]. Thus, there is promise for XN to positively impact clinical activity in CD in a safe manner via multiple relevant mechanistic pathways. This trial will determine whether these mechanisms of XN translate to humans based on the clinical activity of CD, inflammatory biomarkers, intestinal permeability, and gut microbial composition. Furthermore, flavonoids have demonstrated modulatory activities relating to platelet function [37]. Therefore, exploring such potential in CD may guide therapeutic considerations in its preventing long-term risk of thrombotic events [38].

Strengths of this trial protocol include its design and the meticulous efforts to ensure data accuracy, participant retention, and safety. The ability to perform direct comparisons of results from the preceding trial in healthy adults supports higher impact and validity of findings in this study. Furthermore, this research is a strong example of inter-disciplinary and cross-institutional collaboration, adding rigor and innovative methods to the study of a natural drug candidate.

We have observed several limitations in the current protocol since commencing this trial. First, the demographic distribution of the Portland, OR metropolitan area is predominantly non-Hispanic white and will limit the generalizability of findings from this trial. Second, the study has faced several challenges that limit recruitment efforts. For example, the population in the Portland area has high usage of several forms of anti-inflammatory compounds prohibited in this study (e.g., *Cannabis* products and turmeric). The COVID-19 pandemic has compounded these challenges for multiple reasons: quarantine regulations encumbered recruitment efforts, national vaccine administration posed restrictions on participant eligibility, and participants with chronic conditions face a disproportionate threat from infection [39]. Furthermore, CD has a relatively low prevalence in the general population which can challenge recruitment penetration. Additionally, the use of a 150-point CDAI cutoff as a tool for determining clinical activity further restricts participant eligibility. Objectively defining “active” disease in this way may dismiss individual participant experience of chronic disease. Finally, this trial is limited by the lack of dietary pattern data, which has the potential to confound data associated with the impacts of XN on the gut microbiome [40].

Nevertheless, this phase II trial will generate a substantial source of data for direct comparison to an otherwise healthy population in the phase I trial. Rigorous investigations into the safety and tolerability of natural drug candidates like XN will support and inform similar trials in the future. While the findings of this trial will be of great interest to clinical translational investigators and healthcare providers, it will also be impactful for patients seeking safe, adjunctive treatments for CD or other chronic inflammatory conditions affected by gut permeability such as rheumatoid arthritis [41, 42].

## Trial status

IRB #RB71720. Approval date: July 17, 2020. Current protocol version: v1.13. Recruitment start date: August 1, 2020. Projected recruitment end date: December 31, 2022. Current enrollment as of April 28, 2022: 15 participants completed of up to 32.

## Data Availability

The data generated by this study will be available upon request to the corresponding author.

## Abbreviations

NCCIH: National Center for Complementary and Integrative Health
NHLBI: National Heart, Lung, and Blood Institute
XN: Xanthohumol
Nrf2: Nuclear erythroid 2-related factor 2
NFκB: Nuclear factor-κ B
FXR: Farnesoid-X receptor
CD: Crohn’s disease
CDAI: Crohn’s Disease Activity Index
FDA: The United States Food and Drug Administration
AST: Aspartate aminotransferase
ALT: Alanine aminotransferase
GGT: ɣ-Glutamyl transferase
eGFR: Estimated glomerular filtration rate
BUN: Blood urea nitrogen
Cr: Creatinine
PROMIS-29: Patient-Reported Outcomes Measurement Information System 29-item questionnaire
FCP: Fecal calprotectin
IND: Investigational new drug
CBC: Complete blood count
CMP: Comprehensive metabolic panel
OHSU: Oregon Health and Sciences University
OCTRI: Oregon Clinical and Translational Research Institute
PI: Principal investigator
DSMB: Data and Safety Monitoring Board
CRFs: Case report forms
CI: Confidence interval
IRB: Institutional review board
NUNM: National University of Natural Medicine
